#### Secondary Outcomes

The secondary outcomes are the distress, caregiver burden, quality of life, and satisfaction with care, assessed by the corresponding scales measured at the beginning and end of each treatment period. Distress will be measured using the Distress thermometer (DT), which is a self-reporting instrument with two parts: a visual image scale ranging from 0 (no distress) to 10 (extreme distress) and a problem list with 36 questions (Riba et al., 2019). Caregiver burden will be measured using the Zarit Burden Interview (ZBI), which is a 22-item self-reporting questionnaire, rated on a five-point Likert scale, from 0 (“never”) to 4 (“nearly always”) (Zarit et al., 1980). QOL will be assessed with the Chinese version of the Medical Outcomes Study 12-item Short Form (C-SF-12), which is a 12-item scale containing eight subscales and two dimensions (Ware et al., 1996). Satisfaction with care will be measured using the Family Carer Satisfaction with Palliative Care scale (FAMCARE-2), which is a 20-item scale developed to measure family members' satisfaction with the delivery of palliative care (Kristjanson, 1993).

### Data Collection

Baseline data will include demographic information, contact details, and psychological assessment. The intervention outcomes including multiple scales, will be measured at the beginning and end of each treatment period. These data will be collected in paper form or WeChat form, which is a popular and convenient social networking application for mobile phones in China. Each participant will be interviewed, followed up and assessed by the specially appointed training nurses using print scales or electronic scales. The electronic scales through WeChat app will be sent to the participants by the training nurses. For the WeChat app, application by ID card of principle investigators for the official account has been submitted, and after obtaining the qualification authorization, the information which had been filled by participants can be checked and downloaded through the account. A database management based on Access 3.0 would be made. Two trained nurses will entry the data when data available. Each data collection takes about 20 min for participants. These data will be entered directly into the electronic trial database.

### Participant Timeline

The study is expected to end on December 31, 2021, and the expected recruitment period is November 2020 to June 2021. Each participant will spend about 5 months from start of his/her individual assessment until the end of the individual treatment, 12 weeks of which are 6 treatment periods and 5 weeks are 5 intervals between different treatment cycles or treatment periods.

### Statistical Methods

For each cycle, each washout periods, and each person, the data from the baseline will be managed to conduct analysis. Outcomes will be analyzed with longitudinal mixed effects models combining baseline and each period's measurements using time, treatment, and a time-by-treatment interaction as fixed effects, and clinician and patient as random effects. A Bayesian multi-level random effects model on the outcome will be used to combine in incorporating serial correlation and other covariates for each participant by WinBUGS software (Spiegelhalter et al., 2003).

Traditional statistical method also will be used. The interactions between the intervention and covariates including age, sex, marital status, education, employment status, etc. will conduct exploratory analyses. The paired *t*-test will be used to compare the continuous quantitative data between the two groups, and the paired chi-squared test will be used to classify the data. The measurement data will be expressed as X ± s. A *P* < *0.05* will be considered statistically significant.

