### Sample Size Calculation

The sample size was calculated based on the previous research of Senn, and according to the power of 80% (Senn, 2002, 2019). The assumption of a minimally important difference of 0.4 SDs on the SAS and SDS interference scale (Liu and Yang, 2019). Assuming a 5% dropout rate, using a 2-group *t*-test with 2-sided alpha equalling 0.05, 300 periods (50 participants and 6 periods for each person) would achieve study objectives.

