### Outcomes

#### Primary Outcome

The primary outcome is the psychological status, assessed by the degree of anxiety and depression measured at the beginning and end of each treatment period. The degree of anxiety and depression will be measured by the SAS and SDS, and both of them are self-report questionnaires with 20 items rated on a four-point scale (Zung, 1965, 1971).

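### The mixed model takes pre-treatment start-of-period scores as outcomes and adds a time-by-treatment term, so the treatment effect and its precision depend on which coefficient is read

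*Protocol article*

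**What the plan says.** Protocol article, Statistical Methods: the outcomes go into longitudinal mixed models "combining baseline and each period's measurements using time, treatment, and a time-by-treatment interaction as fixed effects", with clinician and patient as random effects. The section does not say what time stands for or which term or contrast is the treatment effect. It also lists a Bayesian multilevel model and a paired t-test, and calls none of the three primary.

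Protocol article, Primary Outcome: psychological status is "assessed by the degree of anxiety and depression measured at the beginning and end of each treatment period". With six periods, each participant therefore gives up to 12 SAS and 12 SDS scores.

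Protocol article, Sample Size Calculation: the target is a "minimally important difference of 0.4 SDs on the SAS and SDS interference scale", at 80% power, "using a 2-group *t*-test with 2-sided alpha equalling 0.05" and 5% dropout. The conclusion is that "300 periods (50 participants and 6 periods for each person) would achieve study objectives". The unit counted is the period, and the quantity is one difference between two interventions.

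**The concern.** A start-of-period score is taken before that period's intervention. With random order and no carryover, its expected treatment difference is zero. It is useful as an adjustment variable, but as an outcome it carries no information on the effect except through its correlation with the end score.

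Once such scores are stacked with the end scores and crossed with treatment, the treatment effect has no single meaning. With time coded 0 at the start and 1 at the end, the treatment coefficient is the start difference and the interaction is the difference in change. With time as a linear period number, the treatment coefficient is the difference at time zero, outside the data if coding begins at 1. These quantities differ in precision, and only some are the simple difference on which the sizing rests. The same data could be reported through any of them, and a real 0.4 SD difference could be missed through an inefficient choice.

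**Working it through.** **Inputs.** From Sample Size Calculation: 0.4 SD, two-sided alpha 0.05, 80% power, 5% dropout, 300 periods (150 per intervention). From Statistical Methods: random effects for clinician and patient, none for period. Assumed, because the protocol does not give them:
- the 0.4 SD is in units of the total SD (set to 1);
- the patient ICC takes values from 0 to 0.5;
- r, the correlation of start and end scores in the same period beyond the patient effect, takes values from 0 to 0.7;
- the clinician effect is ignored.

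**1. The plan's own figure.** A two-group comparison at 0.4 SD and 80% power needs 99 periods per intervention (normal approximation; 100 by the exact t-test). That is 198 in all, and 198/0.95 = 208.4, so 209. The stated 300 is not reproduced. With 150 per intervention, z = 0.4 × √(150/2) = 0.4 × √75 = 3.464, and power = Φ(3.464 − 1.96) = 93.4%. This is the reference below.

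**2. Time as start/end.**
- End-of-period contrast (treatment + interaction): variance ∝ (1 − ICC), so power = Φ(3.464/√(1 − ICC) − 1.96).
- Interaction alone: variance ∝ 2(1 − ICC)(1 − r).
- Ratio of standard errors = √(2(1 − r)), whatever the ICC. At r = 0, which is what the listed random effects imply, it is √2 = 1.41.

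| ICC (r = 0) | End-of-period contrast | Interaction |
|---|---|---|
| 0 | 93.4% | Φ(3.464/1.414 − 1.96) = 68.8% |
| 0.2 | 97.2% | 78.2% |
| 0.3 | 98.5% | 83.3% |
| 0.5 | 99.8% | 93.4% |

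A generalised least squares calculation for 50 people × 6 periods × (start, end) gives the same values.

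**3. Effect of r, at ICC 0.** The last column constrains the start scores to have no treatment difference, which has the same power here as using the start score as a covariate.

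| r | SE ratio | Interaction | End only | Start scores constrained |
|---|---|---|---|---|
| 0 | 1.41 | 68.8% | 93.4% | 93.4% |
| 0.3 | 1.18 | 83.3% | 93.4% | 95.3% |
| 0.5 | 1.00 | 93.4% | 93.4% | 97.9% |
| 0.7 | 0.77 | 99.4% | 93.4% | 99.8% |

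The interaction overtakes the end-only contrast above r = 0.5. The constrained analysis is never worse than either.

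**4. Time as linear period number.** The variance of the treatment coefficient at time zero is inflated by 1 + mean(t)²/var(t). For t = 1 to 6 the mean is 3.5 and the variance 35/12 = 2.917, so the factor is 1 + 12.25/2.917 = 5.2 and the standard error ratio √5.2 = 2.28. Power at ICC 0 is Φ(3.464/2.28 − 1.96) = 33%. At ICC 0.5, with the person-level structure included (ratio about 2.3), it is 57%. Coded 0 to 5, the factor is 3.14 and power at ICC 0 is about 50%. These figures use one end score per period. If the start scores are stacked as well, the coefficient averages a zero start difference with the end difference and is also halved.

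**The case against.** A reader might infer that no coefficient of this model gives the sized effect, and that power falls to about 32–69%. The document does not support either statement.

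- The end-of-period difference is in the model. It is treatment plus interaction, or the treatment coefficient itself if end is the reference time, at full power (93.4% at ICC 0). The loss comes from reading another coefficient.
- With random order and no carryover, the interaction has the same expected value as the end-score difference. It is not biased, and at high within-period correlation it is the more precise of the two.
- The 69% is the value at zero start–end correlation, a floor among non-negative correlations and unlikely for repeated self-report scales. The value near 32% needs linear period coding, read at time zero. Centring time removes that inflation, and the text does not say that time is coded this way.
- The protocol does not call this model primary, does not say that 0.4 SD is an end-of-period difference, and states 80% power, not 93%. Measuring at both ends of the period is compatible with an analysis of change.
- Coding and contrasts are often left to an analysis plan, and modelling baseline as part of the response is an accepted longitudinal method.

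All but the last point stand in full and limit the size of the finding. The last stands in part: silence on coding alone would be no finding. But the article prints the fixed effects, with start scores among the outcomes and treatment free to differ at the start. That is a stated method, and it does not match the stated sizing. The accepted form of baseline-as-response constrains the start difference to zero; the printed terms include no such constraint.

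It is also tempting to say that the patient random effect closes the gap. It raises the power of both contrasts but leaves their ratio at 1.41. Only correlation within a period, for which no random effect is listed, narrows it.

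**Conclusion.** The point holds in limited form. The model treats pre-treatment scores as outcomes and crosses them with treatment, while the sizing is for one simple difference, so the reported effect and its precision depend on an unstated choice. With start/end coding and the listed random effects, reading the interaction costs a factor of 1.41 in standard error: 69% against 93% power at ICC 0, and 78% against 97% at ICC 0.2. The cost falls to nothing at a within-period correlation of about 0.5 and reverses beyond it. With linear period coding 1 to 6, the treatment coefficient has power of about 33% at ICC 0 and 57% at ICC 0.5.

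These are conditional illustrations: they assume 300 complete periods, 0.4 total SD, no carryover, and coding and correlations that the protocol does not give. They do not show that the trial is underpowered, because the end-of-period contrast can be recovered from the written model. They do show that the choice matters enough to fix before the data are analysed.

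**What to change.** - Make the end-of-period SAS score and the end-of-period SDS score the analysed outcomes.
- Fit treatment and period (1–6, categorical) as fixed effects, keep the clinician and patient random effects, and name the treatment coefficient as the primary estimate.
- Bring in the start-of-period score as a covariate, or keep it in the response with its treatment difference constrained to zero. Either relies on no carryover, so also use the start scores to check for it.
- Make time-by-treatment secondary, and define time there.
- State in the sample size section that the 0.4 SD refers to this contrast, and which SD is meant.

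The cost is analysis wording only: no new data, visits or participants.

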## Abstract

**Background:** Both anxiety and depression in family caregivers (FCs) of advanced cancer patients are common, and they have a negative influence on both the FCs and the patients. Some studies suggested that a variety of interventions could alleviate the psychological symptoms of FCs. However, there is no consensus on much more effective methods for intervention, and relatively high-quality research is blank in psychological problems of these population in China. The validity of mindfulness-based stress reduction (MBSR) and psychological consultation guided by the needs assessment tool (NST) in the psychological status of caregivers will be compared in this study to select a more suitable intervention for the FCs of advanced cancer patients in China.

**Methods and Analysis:** A randomized N-of-1 trial would be conducted at the Cancer Hospital, Chinese Academy of Medical Sciences. Fifty eligible FCs of advanced cancer patients will be recruited, and all will receive three cycles of psychological intervention treatment, with each cycle including both of MBSR and psychological consultation guided by the NST. MBSR and psychological consultation guided by the NST will be compared with each other in each cycle, and the intervention sequence will be based on the random number table generated after the informed consent has been completed. Each treatment period is 2 weeks, and the interval between different treatment cycles or treatment periods is 1 week. The self-reported scales are measured at the beginning and end of each treatment period, including the Self-Rating Anxiety Scale (SAS), the Self-Rating Depression Scale (SDS), Distress Thermometer (DT), Zarit Burden Interview (ZBI), Chinese version of the Medical Outcomes Study 12-item Short Form (C-SF-12), and Family Carer Satisfaction with Palliative Care scale (FAMCARE-2).

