N-of-1 trials, which are within-patient randomized multi-period crossover trials that compare two different therapeutic strategies, provide the highest level evidence of intervention effects for individuals, and enhance precision when intervention effects are heterogeneous between individuals (Mirza and Guyatt, 2018; Porcino et al., 2020). At least 2 cycles with 4 periods are needed to compare the effectiveness and give much more accurate. In our study, because of the high quality of compliance, 3 cycles with 6 periods are designed and are available.

Therefore, we plan to conduct this study through an N-of-1 trial, in which the bias resulting from the difference between individuals can be minimized to the greatest extent. In the protocol, the design of this N-of-1 trials is given in detail. The main purpose of the study is to compare the effect of MBSR and psychological consultation guided by the NST on the psychological well-being and QOL of FCs of advanced cancer patients.

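### The mixed model as written has no participant-by-treatment random effect, so with one outcome per period its standard error for the average effect among caregivers generally is too small if individual effects vary

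*Protocol article*

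**What the plan says.** Statistical Methods specifies a longitudinal mixed model with fixed effects for time and treatment, plus "a time-by-treatment interaction as fixed effects, and clinician and patient as random effects". A second model follows: "A Bayesian multi-level random effects model on the outcome will be used to combine in incorporating serial correlation and other covariates for each participant". The article does not say which of its effects are random. A paired t-test "will be used to compare the continuous quantitative data between the two groups"; its unit of analysis is not stated. Treatment-by-covariate interactions (age, sex and others) are exploratory.

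The Introduction says that N-of-1 trials "enhance precision when intervention effects are heterogeneous between individuals", and adds, for this trial, that "the bias resulting from the difference between individuals can be minimized to the greatest extent". The Abstract gives the purpose as "to select a more suitable intervention for the FCs of advanced cancer patients in China". On size, the Introduction says that "3 cycles with 6 periods are designed and are available", and Sample Size Calculation says that "300 periods (50 participants and 6 periods for each person) would achieve study objectives".

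**The concern.** Every participant receives each intervention three times. If the MBSR-minus-consultation effect differs between caregivers, a person's three within-cycle differences all carry that person's own effect and are not independent evidence about the average. A patient random effect read as an intercept absorbs differences in level between people, not differences in response to treatment. The model then treats the cycles as more independent than they are.

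At stake are the p-value and confidence interval for the average comparison, if the result is to guide care beyond the 50 people studied. A mixed model with these terms also yields no individual treatment effects, apart from what the exploratory covariate interactions explain.

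**Working it through.** **Inputs from the protocol article.** 50 participants, 3 cycles and 6 periods each; minimally important difference 0.4 SD; two-sided alpha 0.05; 5% dropout (50 × 0.95 = 47.5, taken as 47).

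**Inputs assumed, because the documents do not give them.** SD of individual treatment effects, τ: 0.2, 0.4 or 0.6. Within-person correlation ρ: 0.5 or 0.7. Both are on a scale where the total SD of a score, leaving out treatment-effect variation, is 1, so the residual variance is σ² = 1 − ρ. One outcome per period, no clinician variance and no serial correlation.

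**The plan's own figure.** The article gives no standard error or error rate for this model, so there is none to reproduce. Its sample size, by the 2-group formula it names, is 2 × (1.960 + 0.842)²/0.4² = 98.1, so 99 per group or 198 periods, and 198/0.95 = 208.4, so 209 after dropout. That is not 300. This is a separate matter and does not enter the argument here. The formula has no variance for individual effects either.

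**True variance.** Code treatment as ±½. One person's mean difference over three cycles has variance 2σ²/3 + τ². Over N people:

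Var(true) = (σ² + 1.5τ²)/(1.5N).

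**Variance reported by a random-intercept model.** The omitted interaction adds 6 × ¼ × τ² = 1.5τ² per person to the within-person sum of squares, spread over 5 degrees of freedom. The residual variance is therefore estimated as about σ² + 0.3τ², and

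Var(model) = (σ² + 0.3τ²)/(1.5N).

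**Type I error** = 2Φ(−1.96/√R), where R = Var(true)/Var(model). For N = 50:

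| ρ | τ | σ² + 1.5τ² | σ² + 0.3τ² | R | Type I error |
|---|---|---|---|---|---|
| 0.5 | 0.2 | 0.560 | 0.512 | 1.09 | 6.1% |
| 0.5 | 0.4 | 0.740 | 0.548 | 1.35 | 9.2% |
| 0.5 | 0.6 | 1.040 | 0.608 | 1.71 | 13.4% |
| 0.7 | 0.2 | 0.360 | 0.312 | 1.15 | 6.8% |
| 0.7 | 0.4 | 0.540 | 0.348 | 1.55 | 11.6% |
| 0.7 | 0.6 | 0.840 | 0.408 | 2.06 | 17.2% |

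Simulations of 4,000 trials per setting gave 6.2%, 9.1% and 13.4% at ρ = 0.5, and 6.9%, 11.9% and 17.4% at ρ = 0.7.

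**Check by fitting the models.** In a small REML run (40 trials) with an effect SD equal to the residual SD, the mean standard error was 0.130 without a random treatment slope and 0.179 with one. The empirical SD of the estimate was 0.180.

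**Paired t-test.** On 150 cycle pairs it uses (2σ² + τ²)/150. At ρ = 0.5, τ = 0.4 that is 1.16/150 = 0.00773, against a true 0.74/75 = 0.00987: ratio 1.28, type I error 8.3%. Over the whole grid it runs from about 6% to 14%. On 50 participant means the simulated error was 5–6% throughout.

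**Power with the correct variance.** At N = 47, ρ = 0.5, τ = 0.4: SE = √(0.74/70.5) = 0.102, 0.4/0.102 = 3.90, power about 97%.

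**The case against.** **The article never says intercept only.** It is a condensed text, and a full covariance structure is often left to the analysis plan. That is fair, but the sentence does list the model's terms, and the natural reading has no treatment slope. It tempers the severity.

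**The Bayesian model may already carry the effect.** It may, and neither analysis is named as primary. A reader might infer that the plan as a whole cannot estimate individual effects; the article does not support that. But the Bayesian model's random effects are not stated, and a slope there would not repair the mixed model.

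**The standard error is not too small in every case.** A reader might infer that it is too small whenever responses differ. That goes too far in two ways.
- For the mean effect in just these 50 people it is not too small: simulated error was about 5%, falling to 2.4% when the effect SD equals the residual SD. The stated aim, however, is caregivers in China.
- Scores are taken at the start and end of each period and might be stacked. With independent residuals, error was still 7–12% at τ = 0.4 to 0.6. With 30% of the variation shared within a period, it was 2% at τ = 0 and 5–9% at τ = 0.4 to 0.6, because the missing period effect pulls the other way.

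**Clinician variance could dilute the problem.** Under Interventions, clinicians deliver the intervention for which they are responsible, so clinician may be nested in treatment. On assumed figures (two clinicians per arm, clinician SD 0.1, variance well estimated), 2 × 0.01/2 = 0.01 is added to both variances. At ρ = 0.5, τ = 0.4 the ratio becomes 0.01987/0.01731 = 1.15 and the error 6.7%. This shows sensitivity; with so few clinicians the variance would be poorly estimated.

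**τ = 0 does not contradict the plan.** The remark on heterogeneity describes N-of-1 trials in general, and the trial-specific reason is reducing bias from differences between people. That stands: the article raises varying effects as a possibility and does not assert them.

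**The paired t-test is not shown to be wrong.** Its unit is unstated, and on participant means it is valid. It needs only to be specified.

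**Conclusion.** The concern holds in a conditional form. It rests on three conditions: effects vary between caregivers, the target is the wider caregiver population, and one outcome per period is analysed. Under these, the mixed model as written understates the standard error of the average effect. At ρ = 0.5, τ = 0.4 the model's SE is 0.0855 against a true 0.0993, about 14% too small.

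The direction is firm under those conditions; the size is illustrative. The excess error is minor at τ = 0.2 and material from about 0.4. The highest figures, 13% and 17%, need τ = 0.6, which is 1.5 times the 0.4 SD difference that the plan treats as important. This is a should-fix point.

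**What to change.** Under Statistical Methods:
- Add a random participant-by-treatment effect (a random treatment slope) to the mixed model.
- State the same effect explicitly in the Bayesian model.
- Specify that the paired t-test uses each participant's mean of the three within-cycle differences (n = 50, 49 degrees of freedom).

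Nothing in the calculation shows a need for a participant-by-cycle effect or a particular degrees-of-freedom method, so neither is asked for.

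The change is to wording only and needs no more participants. Its cost is modestly wider intervals if effects vary: in the setting of the verdict, 0.0993/0.0855 = 1.16, about 16% wider. Settling the term before the data are seen also avoids a later choice between two standard errors for the same comparison.
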